# Tuberculosis (TB) Aftermath: study protocol for a hybrid type I effectiveness-implementation non-inferiority randomized trial in India comparing two active case finding (ACF) strategies among individuals treated for TB and their household contacts

**DOI:** 10.1186/s13063-022-06503-6

**Published:** 2022-08-05

**Keywords:** Tuberculosis, Recurrence, Active case finding, India, Hybrid effectiveness-implementation trial

## Abstract

**Background:**

Approximately 7% of all reported tuberculosis (TB) cases each year are recurrent, occurring among people who have had TB in the recent or distant past. TB recurrence is particularly common in India, which has the largest TB burden worldwide. Although patients recently treated for TB are at high risk of developing TB again, evidence around effective active case finding (ACF) strategies in this population is scarce. We will conduct a hybrid type I effectiveness-implementation non-inferiority randomized trial to compare the effectiveness, cost-effectiveness, and feasibility of two ACF strategies among individuals who have completed TB treatment and their household contacts (HHCs).

**Methods:**

We will enroll 1076 adults (≥ 18 years) who have completed TB treatment at a public TB unit (TU) in Pune, India, along with their HHCs (averaging two per patient, *n* = 2152). Participants will undergo symptom-based ACF by existing healthcare workers (HCWs) at 6-month intervals and will be randomized to either home-based ACF (HACF) or telephonic ACF (TACF). Symptomatic participants will undergo microbiologic testing through the program. Asymptomatic HHCs will be referred for TB preventive treatment (TPT) per national guidelines. The primary outcome is rate per 100 person-years of people diagnosed with new or recurrent TB by study arm, within 12 months following treatment completion. The secondary outcome is proportion of HHCs < 6 years, by study arm, initiated on TPT after ruling out TB disease. Study staff will collect socio-demographic and clinical data to identify risk factors for TB recurrence and will measure post-TB lung impairment. In both arms, an 18-month “mop-up” visit will be conducted to ascertain outcomes. We will use the RE-AIM framework to characterize implementation processes and explore acceptability through in-depth interviews with index patients, HHCs and HCWs (*n* = 100). Cost-effectiveness will be assessed by calculating the incremental cost per TB case detected within 12 months and projected for disability-adjusted life years averted based on modeled estimates of morbidity, mortality, and time with infectious TB.

**Discussion:**

This novel trial will guide India’s scale-up of post-treatment ACF and provide an evidence base for designing strategies to detect recurrent and new TB in other high burden settings.

**Trial registration:**

NCT04333485, registered April 3, 2020.

CTRI/2020/05/025059 [Clinical Trials Registry of India], registered May 6 2020.

**Supplementary Information:**

The online version contains supplementary material available at 10.1186/s13063-022-06503-6.

## Administrative information

Note: the numbers in curly brackets in this protocol refer to SPIRIT checklist item numbers. The order of the items has been modified to group similar items (see http://www.equator-network.org/reporting-guidelines/spirit-2013-statement-defining-standard-protocol-items-for-clinical-trials/).

## Introduction

### Background and rationale {6a}

#### Disease burden

Over four million people who developed tuberculosis (TB) worldwide in 2020 were never diagnosed and linked to care. The missing four million are among an estimated 9.9 million new or recurrent cases, of which 1.5 million died. India has the largest TB burden in the world, with over 2.5 million cases and approximately half a million deaths each year [1]. Further, it is estimated that nearly a quarter of the world’s missing cases are in India. TB control is a priority for the Indian government and they have set an ambitious target to eliminate the disease by 2025 [2]. Despite a 24% reduction in incidence over the past decade [3], an increase in cases is expected due to pandemic-related setbacks [1, 4]. Specifically, models of interruptions in TB services due to COVID-19 project an increase of 182,000 TB cases and 83,600 TB deaths in India between 2020 and 2025 [5]. As part of their response, the Indian Government has released modified recommendations for detecting and treating TB in the context of COVID-19 [6, 7]. Scale-up of TB preventive treatment (TPT) is also being prioritized and is now recommended for all household contacts (HHCs) in India after ruling out TB disease [8]. However, to tackle India’s TB epidemic, optimized active case finding (ACF) strategies that specifically target high-risk populations will also be needed.

#### Recurrent TB

Individuals who recently completed TB treatment are a high-risk group who should be targeted for ACF. Recurrent TB arises from either endogenous reactivation (relapse) or exogenous reinfection and people who have been treated for TB are at risk for both [9–11]. Despite a rise in treatment success rates from 69 to 86% over the past two decades [1, 12], recurrent TB still accounts for approximately seven percent of reported TB cases worldwide [13, 14]. In addition, persistent social or biological risk factors among individuals who have had TB once place them at increased risk of getting reinfected and developing TB again [15, 16]. Recurrent TB poses a threat to control programs, as it is associated with lower cure rates than new TB [17], drug resistance [18, 19], and expensive retreatment regimens which can further exhaust national budgets for TB control [20].

In India, TB recurrence is particularly common; a meta-analysis of seven studies documented an overall recurrence rate of approximately 10% [21]. A more recent study showed that 13% of cured and treatment completed patients developed recurrent TB within 1 year of treatment end, for a weighted recurrence rate of 12.7/100 person-years [22]—a TB incidence rate that is over 60 times the national average. That same review concluded that routine follow-up of all TB patients for 1 year after treatment completion may be an efficient mechanism for identifying new cases of TB. Recent TB patients are also a point of contact with another group at elevated risk for TB: their household contacts. In a systematic review and meta-analysis, HHCs of patients with TB in low- and middle-income settings had a 3% TB prevalence at the time of initial contact investigation and a TB incidence of 1500 per 100,000 in the subsequent year [23].

#### Rationale for active case finding among treated TB patients

Directing surveillance resources towards “adequately” treated patients at high risk for recurrent disease is supported by the finding that such patients experience TB risks comparable to other subgroups already targeted by ACF. Although it is clear that the burden of recurrent disease among recently-treated patients is high, evidence for (or against) the effectiveness of ACF in this population is scarce. To date, there are no published ACF trials targeting treated TB patients and their HHC. As a result, the 2021 World Health Organization (WHO) guidelines for systematic screening for TB disease could make only a conditional recommendation that individuals previously treated for TB should be screened in high-incidence settings (≥ 100 cases per 100,000 people) [24]. However, the potential impact of ACF is high. A recent modeling study in South Africa suggests that ACF for recurrent TB would reduce average duration of TB from 9.7 to 5 months among previously-treated TB patients, with a tremendous potential impact on transmission [25]. From a feasibility standpoint, people treated for TB are an ideal population for ACF as they were recently traceable for at least 6 months of TB treatment, making them easier to locate.

#### Which patients develop recurrent TB?

Identifying TB patients likely to develop recurrent disease could help target case-finding efforts and addressing modifiable risk factors could reduce the risk of recurrence. Prior studies have found an association between poor adherence to TB treatment and early recurrence suggestive of relapse [26, 27]. HIV is also a well-recognized risk factor for TB recurrence [10, 28, 29]. Diabetes is associated with a threefold higher risk of TB disease [30] and may be associated with recurrence as well [31, 32]. Alcohol consumption and exposure to tobacco smoke have both been shown to correlate with recurrent disease [28, 33–36]. Similarly, there is evidence that indoor air pollution increases risk of TB disease [37, 38]. Clinically, the pulmonary TB and lung impairment dynamic may be a vicious cycle; treated TB patients with pulmonary sequelae may be at higher risk of chronic lung diseases and subsequently recurrent TB [39]. Finally, socio-economic status and poverty are strongly linked to TB and likely impact risk of recurrence [40–42].

#### Understanding implementation of ACF among treated TB patients

Following former patients for recurrent TB disease presents challenges of clinic-to-community continuity and coordination. Notable examples of using community health workers for ACF in TB programs suggest that this model can be successful [43–45]. Despite these successes, a clear understanding of aspects of optimal implementation is lacking. As a result, multiple examples of under-delivery stand in contrast to the successful use of integrated clinic-community programs [46–49]. Through qualitative and quantitative measures, implementation science provides tools to describe HCW and patient perceptions, management, and role concordance, all of which are used to develop systematic management and implementation strategies. These assessments are vital to guide future implementation.

#### Rationale for comparing home-based vs. telephonic ACF

India’s National TB Elimination Program (NTEP) is dedicated to rolling out a strategy for ACF among treated TB patients; however, they have not yet defined the strategy they will utilize. In Maharashtra, one of the highest TB burden states in India [50], NTEP policymakers and implementers are enthusiastic about studying the effectiveness of telephonic active case finding (TACF) and home-based active case finding (HACF). HACF strategies have been successful at identifying high proportions of TB among HHCs in high incidence settings [51–53]. However, HACF may be resource-intensive and difficult to scale. Thus, a TACF strategy should be tested. Our hypothesis is that those who need screening will be identified through TACF at a fraction of the cost of HACF. The diagnostic yield is anticipated to be high with both strategies, but differences in proportions of patients and households (HHs) screened, timeliness of the screening and associated costs are not known. TB Aftermath will help determine the most effective and cost-effective of these two post-treatment ACF strategies. Our hybrid type 1 effectiveness-implementation design includes implementation assessments of these strategies, at least one of which will be recommended for rollout in India. This novel trial aligns with the current NTEP strategy and has the potential to guide case detection strategies in India and other high TB burden settings.

#### Objectives {7}

The overall purpose of TB aftermath is to compare the effectiveness, cost-effectiveness, and feasibility of two ACF strategies for detecting recurrent TB and provide evidence needed to implement and scale up the preferred ACF strategy. Our specific objectives are:To conduct a non-inferiority randomized trial to measure the comparative effectiveness of two potentially implementable ACF strategies within the NTEP, conducted by existing NTEP healthcare workers (HCWs): (i) home-based ACF (HACF) and (ii) telephonic ACF (TACF)To characterize implementation processes of the ACF strategies using the RE-AIM framework to inform their future scale-up and sustainability [54]To model the impact and cost-effectiveness of the ACF strategies evaluated in the trial, and of potential alternative strategies for the targeting and timing of those strategiesTo measure the association of the severity, chronicity, and progression of post-TB lung impairment with recurrent TB disease

#### Trial design {8}

TB Aftermath is a hybrid type I effectiveness-implementation non-inferiority trial with individual randomization. A hybrid type I study is defined by Curran et al. as “testing a clinical intervention while gathering information on its delivery during the effectiveness trial and/or on its potential for implementation in a real-word situation.” [55] The participant allocation ratio between the HACF arm and the TACF arm is 1:1.

## Methods: participants, interventions, and outcomes

### Study setting {9}

The study will be conducted in three rural and three urban TB Units (TUs) of the NTEP in Pune district, Maharashtra, India. Each of the six participating TUs has the capacity to diagnose TB, initiate treatment, monitor TB treatment outcomes, and serve as directly observed therapy (DOT) centers. Each TU serves a population of approximately 300,000 to 500,000 people. Current responsibilities of existing TU HCWs include diagnosing TB suspects, linking newly diagnosed patients to TB care, visiting HHs within 7 days of index patient treatment initiation, screening HHCs for TB symptoms, referring potentially eligible HHCs for TPT, providing counseling on infection control, ensuring treatment adherence, and finding patients that are lost-to-follow-up. These responsibilities may be distributed among several positions. Urban TUs are usually staffed by a senior TB treatment supervisor (STS), senior TB laboratory supervisor (STLS), lab technician, and a TB home visitor, whereas rural TUs are only staffed by STS and STLS. For this trial, the role of selected NTEP HCWs will be extended to include additional follow-up on patients and HHs beyond treatment.

### Eligibility criteria {10}

The following criteria applies to enrolment of index patients with TB:

Inclusion criteria:Adults (≥ 18 years of age) who are registered at one of the participating TUs as TB treatment completed or cured (regardless of type of TB or duration of treatment)Confirmed treatment completion status by the referring medical officer of the participating TUDate of treatment completion within 60 days of date of study enrolmentAbility and willingness of participant or legal guardian/representative to provide informed consent to participate in the HACF or TACF arm

Exclusion criteria:Completed TB treatment at a private sector clinic or TU outside of the study (final visit not registered at one of the participating TUs)Actively on TB treatment

There will be no exclusion criteria according to sex/gender, HIV status, type of TB, or racial/ethnic group. For enrolment of HHCs, all individuals, regardless of age, who are able and willing to provide informed consent are eligible to participate.

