#### Criteria for discontinuing or modifying allocated interventions {11b}

Participants may withdraw from the study at any time due to personal reasons. In such cases, the participant’s record while in the study will be maintained along with a progress note describing reason for withdrawal. A participant’s allocated arm may not be modified at any time during the study.

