### Recruitment {15}

On a monthly basis, study staff will review NTEP registers to identify all potentially eligible participants nearing the end of their TB treatment at participating TUs. Patients for whom treatment was extended will also be tracked. All potential trial participants will be contacted and screened for enrolment with 60 days of treatment completion. For both index TB cases and HHCs who do not agree to participate, reasons will be documented and discussed by study staff. Accrual reports will be reviewed regularly and additional TUs will be added if required to achieve target sample size.

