### Assignment of interventions: allocation

#### Sequence generation {16a}

Trial randomization will be computer-generated, using permuted blocks of equal size with balancing by participating TU.

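### Enrolment is not limited to one index patient per household, so one home can be randomised to both arms

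*Protocol article*

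**What the plan says.** **Unit of randomisation.** Trial design {8} describes a "non-inferiority trial with individual randomization" and adds: "The participant allocation ratio between the HACF arm and the TACF arm is 1:1". Sequence generation {16a} specifies allocation "using permuted blocks of equal size with balancing by participating TU". Household plays no part in the allocation.

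**Unit of delivery.** In the data collection section {18a}, the home-based arm has the health worker visit the home at 6 and 12 months and screen the index patient and the contacts. In the telephone arm the index patient is called and is also asked about symptoms in the rest of the household.

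**Who may enter.** Eligibility criteria {10} admit any adult registered as cured or treatment completed at a participating unit, within 60 days of completion. There are two exclusions: treatment completed outside the study units, and being on treatment. For contacts the rule is: "For enrolment of HHCs, all individuals, regardless of age, who are able and willing to provide informed consent are eligible to participate". Under Recruitment {15}, "study staff will review NTEP registers to identify all potentially eligible participants nearing the end of their TB treatment at participating TUs".

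**Nearest thing to a safeguard.** Section {11b} says that a participant's "allocated arm may not be modified at any time during the study".

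**The concern.** Suppose two adults of one home are both treated at a study unit. Under the rules as written each qualifies as an index patient, each is also the other's household contact, and they are randomised independently. About half of such pairs will be split. The same can happen when an enrolled contact develops TB, completes treatment during recruitment and then meets the index criteria.

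In a split home the health worker visits under one allocation and telephones under the other. Three things follow:

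- The telephone-arm patient is also screened face to face. If telephone screening truly finds fewer cases, the shortfall shrinks, and in a non-inferiority trial that leans toward the favourable conclusion.
- A shared contact has two arms and possibly two start dates, because the 12-month window of the primary outcome runs from the index patient's completion date.
- A child under 6 in such a home enters both denominators of the secondary outcome, and preventive treatment prompted by a home visit can be credited to the telephone arm.

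An analysis rule can remove duplicate records. It cannot undo exposure to both strategies.

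**Working it through.** The plan gives no figure for households with two index patients, so there is none to reproduce. The steps below bound the number.

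**Inputs from the article.** 1076 index patients (538 per arm) and 2152 contacts, two per index patient; 12 and 1 TB cases per 100 person-years; 1–2% of contacts developing TB during the study; about 10% of contacts under 6; about 70 eligible children per arm (all Sample size {14}). Contacts "had a 3% TB prevalence at the time of initial contact investigation" (Recurrent TB). Recruitment runs from January 2021 to about February 2023, roughly 24 months (Trial status). Expected cases: 1076 × 0.12 + 2152 × 0.01 = 129.1 + 21.5 = 150.6.

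**Route A: a second case already present when the first is treated.**
- Ceiling: 1 − 0.97² = 5.9%, and 0.0591 × 1076 = 64 homes (or 0.03 × 2152 = 65 contacts). This counts children, people treated elsewhere and people never enrolled.
- Assume 50–80% are adults finishing at a study unit in the window: 32–51 pairs.
- Allow also for the chance that the second patient is enrolled. Six units serving 300,000–500,000 each cover 1.8–3.0 million people. The article puts 12.7 per 100 person-years at over 60 times the national average, so that average is at most 12.7/60 = 0.21. This gives about 3,800–6,350 cases a year, or 7,600–12,700 in two years. Assume half are adult public-sector completers: 3,800–6,350 eligible, of whom 1076 is 17–28%. Then 0.17 × 32 = 5 and 0.28 × 51 = 14 pairs.

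**Route B: a contact who develops TB after enrolment.** 1–2% of 2152 is 22–43. Assume entry uniform over 24 months, onset uniform over 12 months and 6 months of treatment. The share finishing before recruitment closes is then (18 − 6)/24 = 0.5, giving 11–22 possible index patients. Children and people not enrolled have not been removed.

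**Split homes and dilution.** With m two-index homes, m/2 are split. A home of three in both arms yields six records, so split homes supply 3m of 3228 records, or m/1076. That equals (m/2)/538, the share of each arm's index patients. If these records contribute equally to both arms, a true difference of 3 appears as 3 × (1 − m/1076).

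| m | Split homes | Share | A true 3 appears as |
|---|---|---|---|
| 5 | 2.5 | 0.5% | 2.99 |
| 11 | 5.5 | 1.0% | 2.97 |
| 14 | 7 | 1.3% | 2.96 |
| 32 | 16 | 3.0% | 2.91 |
| 51 | 25.5 | 4.7% | 2.86 |
| 65 | 32.5 | 6.0% | 2.82 |

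Even with 11 pairs, the chance that none is split is 0.5¹¹ = 0.0005.

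**Shared contacts.** With one shared contact per two-index home, 11–65 people are duplicated. At 1 per 100 person-years they yield 0.1–0.65 cases, so what is duplicated is mostly person-time. For the secondary outcome, 32 split homes × 10% is about 3 shared children at the ceiling, against about 70 per arm.

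**The case against.** The strongest reply is that this is a small gap in a condensed article. The full protocol is not shown and may contain a household rule. The article does collect household geocodes, the names of young contacts and a contact's telephone number, so overlaps could be found. The shift in the estimated difference is small against a margin of 3. All of that stands. It limits the size of the point but does not remove it: the eligibility rules are stated affirmatively, and as stated they permit the overlap. Finding an overlap later does not reverse the dual exposure.

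Other provisions do not close the gap. The bar on conflicting studies {11d} concerns other trials. The registry match in the mop-up looks for TB diagnoses. The household random effect in {20a} is stated for the risk-factor model and does not assign an arm.

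A reader might infer three stronger things.

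- *Every recurrence in a co-enrolled index patient is counted twice* (64–102 people × 0.12 = 8–12 of about 151 cases). The text does not support this. Outcomes {12} and section {20a} count recurrent TB for index patients and new TB for contacts, so such a recurrence is an index event.
- *3–5% of telephone-arm households would be screened at home.* That rests on the assumed 50–80% and leaves out whether the second patient enrols. It also takes routine contact screening as performed, whereas the sample size section reports about 30% of child contacts in Pune screened and started on treatment or preventive therapy.
- *An index patient who recurs and is retreated would be randomised again.* The rule in {11b} argues against it. It is less clear for contacts, who are not themselves randomised.

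**Conclusion.** The point holds as a design gap of modest size. Individual randomisation, household-level delivery and the absence of a one-index-per-household rule together allow a home to sit in both arms. The number of such homes is not in the documents. Under the assumptions shown it runs from about 3 to about 32 split households, 0.5% to 6% of the 538 per arm, and the upper end is a ceiling. Correlated consent within homes or higher local incidence would raise the lower figures.

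The effect on the primary comparison is a slight pull toward non-inferiority that is unlikely to decide the result by itself. Double counting mainly concerns shared contacts and their person-time. The case for acting is that the change is cheap and that dual exposure cannot be repaired in the analysis.

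**What to change.** In Eligibility criteria {10}, allow one index patient per household and no re-enrolment as an index patient. At screening, check the address and household list against homes already enrolled. A treated adult from an enrolled home is not randomised but is followed under that home's existing allocation.

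For homes already enrolled, identify overlaps before analysis and count each person and each TB episode once, in the arm of the first enrolled index patient. For a second index patient already allocated to the other arm this overrides that person's own draw. The number of such patients should therefore be reported, with a sensitivity analysis as randomised.

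The cost is one eligibility line, an address check, and a small number of otherwise eligible index patients who must be replaced from the registers. The target sample size does not change.
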